**Alternate hypothesis:**

School-based health promotion intervention will decrease the dietary intake of salt (g/day) and sugar (g/day), increase the intake of fruits (g/day) and vegetables (g/day), and decrease the physical inactivity (%) and tobacco and alcohol use (%) among adolescents.

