**Study Design**

Study design is Cluster Randomized Controlled Trial. Each school will be one cluster.

Schools will be randomized to intervention and control group and net changes in the knowledge and practices related to chronic disease risk factors among students, their parents and teachers will be computed by measurements before starting the health promotion intervention and after implementation of the intervention in both intervention and control clusters.

Research approach will be mixed methods: It will have both qualitative & quantitative data. Quantitative data will be collected using validated tools. Qualitative data will be collected by carrying 10 focused group discussions with students, their parents and teachers separately to understand their perception about risk factors and lifestyle behaviors (2 with male teachers, 2 with female teachers, 2 with female students, 2 with male students and 2 with parents in government schools).

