**Formula used:**

**c = 1 + f [ π_0_(1 - π_0_)/m + π_1_(1 - π_1_)/m + k^2^ (π_0_^2^ + π_1_^2^) ] / (π_0_ - π_1_)^2^**

Where,

- c is the number of clusters per treatment arm
- f = 7.84 for 5% type I error and 80% power
- π_1_ is the expected proportion in the intervention arm
- π_0_ is the expected proportion in the control arm
- m is the number of individuals in each cluster (assumed equal in all clusters)
- k is the coefficient of variation in the (true) rates or proportions between clusters in each treatment arm

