**Methods for Objective 3:**

Effectiveness of the intervention will be measured using following indicators in the baseline and end line sample survey among adolescents:

Before the intervention, perceptions, knowledge and practice of case and control group adolescents will be assessed for the chronic diseases and their risk factors with the help of a questionnaire. This will help in measuring the extent of behavior change. This questionnaire will be used as one parameter to assess the effectiveness of the intervention as the same questionnaire will be used after the completion of the intervention. This will help in assessing the improvement of the perception, knowledge and practices.

For objective measurements, anthropometric measurements, such as, height and weight, along with physiological measurement (blood pressure), biochemical measurement (24-hour excretory sodium through spot urine samples) will be taken before and after intervention. This will be the second parameter to assess the effectiveness of the intervention. The net changes in primary and secondary outcome measures among parents and teachers will be considered as exploratory analysis,

| **Intervention** | **Impact** | |
| --- | --- | --- |
|  | **Direct** | **Indirect** |
| Diet | Participant | Family |
| Physical activity | Participant | Family |
| Alcohol | Participant | Family |
| Smoking | Participant | Family |

**Table:** Impact of different interventions on the participants and their families.

| **Expected outcome of Intervention** |
| --- |
| 1. Increase in knowledge about various chronic diseases and their risk factors 2. Positive response for behavior for diet and physical activity 3. Increase in normal BMI and waist-hip ratio 4. Reduction in risk factors of chronic diseases, such as, decrease in salt and sugar intake and increase in iron intake. 5. Reduction in the consumption of junk food. 6. Adherences to the medicine among those having chronic diseases. 7. Change in stage of behavior |

**Table:** Expected outcomes of intervention package

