**Statistical Analysis**

Descriptive statistics such as mean, standard deviation, student’s t-test, will be done separately for both the sexes. Chi-square test will be done for categorical variables. Change in various indicators will be computed in intervention and controls. Multivariable regression will be done to measure the effect of intervention after controlling for the confounding variables, if any. All the statistical analysis will be done using Statistical Package for Social Sciences (SPSS) or R.

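### The effect is framed as net pre-post change with an open covariate rule; the endline comparison should be adjusted for baseline with covariates fixed in advance, a modest gain in precision at no cost in data

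*Protocol*

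**What the plan says.** Two sections describe the effect in terms of change. Study Design says that "net changes in the knowledge and practices related to chronic disease risk factors among students, their parents and teachers will be computed by measurements before" and after the intervention, in both arms. Statistical Analysis says "Change in various indicators will be computed in intervention and controls". Methods for Objective 3 also speaks of net changes for parents and teachers, as exploratory.

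On adjustment, Statistical Analysis says: "Multivariable regression will be done to measure the effect of intervention after controlling for the confounding variables, if any". No confounder is listed. The section does not say whether the regression models the change or the endline value, and it does not mention the baseline value of the outcome as a covariate. The other methods it names are descriptive statistics and t-tests by sex, and chi-square tests.

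The baseline data exist. Methods for Objective 3 says that "the same questionnaire will be used after the completion of the intervention" and that "biochemical measurement (24-hour excretory sodium through spot urine samples) will be taken before and after intervention"; height, weight and blood pressure are handled the same way.

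The outcomes are of two kinds, as the alternate hypothesis shows: "decrease the dietary intake of salt (g/day) and sugar (g/day), increase the intake of fruits (g/day) and vegetables (g/day), and decrease the physical inactivity". Besides these it names the use of alcohol and of tobacco. Inactivity and these two are expressed as percentages; the intakes are in g/day.

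**The concern.** When an outcome is measured before and after in a randomised trial, a change score subtracts the whole baseline value, whereas a regression of endline on baseline subtracts only the part that predicts endline. If the correlation is weak, as it may be for questionnaire measures of diet and activity, full subtraction adds noise. With only twelve schools, precision is scarce and chance differences between arms at baseline are likely. A change score over-corrects for such differences.

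The second strand is the covariate rule. In a randomised comparison any baseline imbalance between arms is due to chance, so adjusting for confounders 'if any' makes the covariate set conditional on something the analyst has yet to find. The reported effect could then depend on which variables were judged to be confounders.

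**Working it through.** **Inputs from the protocol.** Six schools per arm and 30 pupils per school (Sample size). The sizing formula compares two expected proportions, one per arm, with "f = 7.84 for 5% type I error and 80% power", and contains no baseline term. The protocol gives no baseline-endline correlation, no standard deviation and no intracluster correlation (ICC), so it has no figure of its own to reproduce on this point. Whether the tabulated cluster numbers follow from the formula is a separate question and is not used here.

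**Assumptions.** Continuous outcome with equal variance at both times; correlation r shown as a range; for the clustered check, ICC 0.05 and effect 0.4 SD.

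**Step 1: large-sample variances, relative to an endline-only comparison.**

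- Change score: 2(1 − r)
- Baseline-adjusted endline: 1 − r²
- Adjusted over change: (1 − r²) / [2(1 − r)] = (1 + r)/2

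| r | Change | Adjusted | Adjusted / change |
|---|---|---|---|
| 0.3 | 1.40 | 0.91 | 0.65 |
| 0.5 | 1.00 | 0.75 | 0.75 |
| 0.7 | 0.60 | 0.51 | 0.85 |
| 0.9 | 0.20 | 0.19 | 0.95 |

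The change score has the larger variance than endline-only when 2(1 − r) > 1, that is, when r < 0.5.

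**Step 2: allow for twelve schools.** Analyse school means. The variance of a school mean is 0.05 + 0.95/30 = 0.0817, so the standard error of an endline-only difference is √(2 × 0.0817/6) = 0.165 SD. Estimating the baseline slope from 10 within-arm degrees of freedom inflates the adjusted variance by 1 + 1/(10 − 2) = 1.125. The adjusted-to-change ratio becomes 1.125 × (1 + r)/2, with r now the correlation of school means. It reaches 1 at r = 2/1.125 − 1 = 0.78. The adjusted test also uses 9 rather than 10 degrees of freedom.

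The school-mean correlation is [0.05 × (school-level r) + (0.95/30) × (individual r)] / 0.0817. Simulated power (400,000 replicates, two-sided 5%):

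| School r | Individual r | School-mean r | Change | Endline only | Adjusted |
|---|---|---|---|---|---|
| 0.5 | 0.3 | 0.42 | 53% | 59% | 62% |
| 0.5 | 0.5 | 0.50 | 59% | 59% | 66% |
| 0.7 | 0.5 | 0.62 | 71% | 59% | 74% |
| 0.8 | 0.7 | 0.76 | 88% | 59% | 88% |

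The gain over change is about 9, 7, 3 and 0 points.

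**Step 3: chance imbalance.** If the school means differ by D at baseline, the change-score estimate has conditional expectation (true effect) + (r − 1)D. For D = 0.165 SD (one standard error) and r = 0.5, the shift is −0.5 × 0.165 = −0.08 SD, against the assumed effect of 0.4 SD. Over all randomisations D averages zero, so there is no bias. Baseline adjustment removes this conditional shift apart from error in the estimated slope.

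**Scope.** Steps 1 to 3 apply to intakes in g/day, blood pressure and sodium. They do not carry over directly to the binary indicators on which the trial was sized. The counterpart there is a model for endline status with baseline status as a covariate.

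**The case against.** The strongest reply is that the protocol does not fix a change-score estimator. The sentence on change says only that it will be computed; the sentence on the effect is about regression, and that regression may well have endline as its outcome and baseline among its covariates. Outcome definition and covariate lists are also commonly left to a statistical analysis plan, which is not shown. This stands as far as it goes: a missing covariate list is not in itself a fault. What remains is that change is the only effect measure the protocol does state, in two sections, and that the one rule it gives for covariates is conditional.

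Four stronger readings are tempting, and the document does not support them.

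- A reader might infer that the planned analysis is biased. A comparison of changes is unbiased under randomisation.
- A reader might infer a sure saving of 15% to 35% in variance from the large-sample ratios at r between 0.3 and 0.7. These rest on assumed correlations, ignore the twelve-school structure and do not apply to binary outcomes.
- A reader might take 'if any' to mean that covariates will be picked after inspecting imbalance. The protocol describes no such procedure; it merely does not rule it out.
- A reader might think that baseline adjustment itself ends covariate selection. Only a list fixed in advance does that, and it would do so equally with change scores.

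It is also fair to say that the absence of any cluster-level analysis in Statistical Analysis is the larger, separate problem.

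**Conclusion.** The point holds as an improvement in efficiency and in robustness to chance imbalance, together with a loosely worded covariate rule; it does not show a bias. For continuous outcomes, baseline adjustment is at least as precise as a change score in large samples. With six schools per arm it gains roughly 3 to 9 power points at low to moderate correlation and essentially nothing once the school-mean correlation is near 0.78; above that, a change score is marginally better. These sizes rest on an assumed ICC of 0.05, an assumed effect of 0.4 SD, equal variances and correlations that the protocol does not supply. The change is worth making because the baseline is already measured and the downside is negligible.

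**What to change.** Replace the sentences on change and confounders in Statistical Analysis with text to this effect:

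> The intervention effect is the between-arm difference at endline, adjusted for the baseline value of the same outcome (baseline status for binary outcomes) and for a named set of covariates fixed before allocation. No covariate will be added because of observed baseline imbalance. Changes from baseline are reported descriptively.

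Delete 'if any' and align Study Design with this wording. Four further points belong with it:

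- Fit the model in an analysis that treats school as the cluster, with degrees of freedom suited to twelve clusters. The protocol does not yet contain such an analysis.
- State that each pupil's baseline and endline records are linked. Methods for Objective 3 refers to sample surveys at the two times and does not say so. If linkage is impossible, adjust for the school's baseline mean.
- If sex is among the covariates, reconcile this with the statement that analyses are done separately for each sex.
- Say how binary outcomes are modelled.

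The cost is wording plus record linkage for consenting pupils. No new measurement is needed. If the adjustment is made at school level, it uses one of ten degrees of freedom.

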**Ethical Considerations**

Permission for conducting the study is taken from Institute’s Ethical Committee (INT/IEC/2018/000082; Date: 22/ 01/2019) and the study is registered under the Clinical Trial Registry of India (CTRI/2019/09/021452; 30/09/2019). During this study the participant’s data will be kept confidential. This study will not cause any harm to participants and they can refuse to participate in the study at any time.

